## Appendix A

The target study population is 320 participants based on the capacity of a teaching kitchen (20 study participants in the TK arm and 20 in the control group times two cohorts at each of four sites). Power calculations using a total sample size of 320 participants indicate that the teaching kitchen intervention is designed to detect a significant improvement in metabolic syndrome biomarkers, with an improvement rate of approximately 31.8% needed in the intervention group to demonstrate a meaningful effect compared to the control group.

Improvement in at least one of the following metabolic markers (fasting plasma concentrations of glucose, insulin, ALT/AST, and lipids including cholesterol, triglycerides, LDL, HDL, and cholesterol HDL cholesterol ratio or the triglyceride HDL cholesterol ratio) after participation in our TK intervention.

Given that:

- There are two arms: control group and intervention group.
- Total sample size is 320.
- Two-sided test.
- Under a significance level of 0.05.

Assume that the percentage of improved study population in the control group is ranging between 5% and 15%.

**Table A1 nutrients-17-00314-t0A1:** Test: Two-Sample Proportional Test.

Assumed Prevalence in Control Group	Proportion Randomized to the Intervention Arm	Minimum Detectable RELATIVE Risk *		Percentage of Improved Study Population in Intervention Group	
		Power = 0.8	Power = 0.9	Power = 0.8	Power = 0.9
5%	0.3	2.95	3.39	14.75%	16.95%
	0.5	2.84	3.21	14.20%	16.05%
	0.7	3.14	3.52	15.70%	17.60%
10%	0.3	2.22	2.46	22.20%	24.60%
	0.5	2.14	2.35	21.40%	23.50%
	0.7	2.29	2.51	22.90%	25.10%
15%	0.3	1.92	2.09	28.80%	31.35%
	0.5	1.86	2.01	27.90%	30.15%
	0.7	1.96	2.12	29.40%	31.80%

Assumed prevalence is the percentage of improved study population; * the ratio of prevalence in the intervention arm over that in the control arm; calculations based on effect estimates as reported in Effectiveness of a Lifestyle Intervention on Metabolic Syndrome. A randomized controlled trial [44].

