#### 2.3.2. Sample Size Estimation

A proposed sample size of 320 participants (4 study sites × 2 cohorts × 20 participants per arm) will have 80% power to detect significant improvements in metabolic syndrome biomarkers ranging from 14.2 to 30.15%, assuming that control group participants have improvements ranging from 5 to 15% for ɑ = 0.05 by using a two-sample *t* test. Power analysis calculations for sample size are based on reported effect size estimates of metabolic syndrome markers (Appendix A) [44].

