#### 2.3.3. Recruitment and Randomization

Potential participants will be recruited through the TK-MT website, paid social media advertisements, physical and digital flyers, social media postings, institutional emails, television spots, ads in community newspapers, booths at health fairs, and referrals from research or clinical staff at the study sites. Study recruitment will follow the process outlined in Figure 1. Preliminary study eligibility will be assessed through an optional pre-screening survey on the TK-MT website followed by a screening phone call.

Alternatively, interested individuals can call the study team directly and complete a phone call screening. Those who are likely eligible based on the phone call screening will complete a follow-up video call with a trained research assistant (RA). These screening methods will collect eligibility data and visually confirm minimal operating kitchen equipment described in the inclusion criteria. The RA will explain the study details and obtain informed consent during these screening calls. Final eligibility will be confirmed by study site PI based on a review of anthropometric data, laboratory data, self-reported medication lists, and study site MD recommendations.

Eligible participants will be randomized at the site level in blocks to either the TK-MT intervention group or the wait-list control group receiving standard care (i.e., followed as usual by their primary care physician). Each site will independently enroll 1–2 cohorts and randomize 28–48 participants to each study arm (for single-cohort sites) or 14–30 participants per arm (for double-cohort sites); the wait-list control group will receive a condensed version of the intervention curriculum after completing the 12-month assessments. Individuals who share a household can participate in this study only if they have separate kitchen workspaces for virtual classes and must be randomized to the same study arm. All recruitment and randomization data will be documented in site-specific REDCap surveys and forms. Incentives, in the form of gift cards and small gifts (notepad, measuring spoons, etc.) valued at a total of USD 200 per individual will be provided after completing (1) laboratory and anthropometric screening, (2) baseline psychometric assessments, (3) 4-month assessments, (4) 12-month assessments, and (5) 18-month assessments.

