##### TK-MT Intervention Curriculum

The TK-MT curriculum is grounded in the social cognitive theory (SCT), which emphasizes the impact of behavioral capability, self-efficacy, and social influences on shaping health behaviors [45]. The curriculum combines observational learning through live modeling demonstrations with hands-on practice and skill-building activities in cooking, nutrition and food literacy, mindfulness, and physical activity. Participants observe instructors and peers, gaining cooking knowledge, skills, and self-efficacy to replicate these behaviors on their own. The TK-MT curriculum fosters self-efficacy by providing opportunities for mastery experiences. Participants receive ongoing feedback, troubleshoot challenges, and gain positive reinforcement as they learn and practice new skills. Successfully planning, preparing, and enjoying healthy meals strengthens their belief in maintaining these behaviors over time. The TK-MT curriculum also fosters a sense of community and social support. Through group discussions and activities, participants learn from and motivate each other. This social interaction builds a support network that can reinforce healthy habits beyond the program duration. By integrating these SCT principles, the TK-MT curriculum seeks to empower participants with the knowledge, self-efficacy, and social support needed to make lasting changes that contribute to a healthier lifestyle.

The TK-MT curriculum is based on the Harvard Healthy Eating Plate [46] and the Substance Abuse and Mental Health Services Administration’s (SAMHSA) Wellness Initiative [47]. The Harvard Healthy Eating Plate emphasizes the importance of consuming a high-quality, diverse diet that is rich in healthy carbohydrates, low in sugary beverages, and incorporates heart-healthy oils [46]. (An overview of the curriculum content can be found in Appendix B). The SAMHSA Wellness Initiative frames wellness as an interconnected, complex concept that functions across 8 different dimensions: emotional, physical, occupational, intellectual, financial, social, environmental, and spiritual [47]. The details of the culinary, nutrition, and lifestyle curriculum components were outlined by the TKC expert multi-day meetings (Appendix C). Mindfulness, physical activity, and behavior change (e.g., goal setting) exercises come from TKC members trained as health coaches and exercise specialists.

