### 2.7. Data Analysis

The primary outcome of feasibility will be assessed through frequency data that are collected on recruitment, attendance, and fidelity. Descriptive statistics (proportions for rates, means, or medians for satisfaction scores) will be used to summarize these measures. We will also document reasons for non-completion (withdrawal or attrition). For surveys addressing participant satisfaction, descriptive statistics (means, medians, proportions, 95% confidence intervals [CI]) will be computed, and data will be analyzed to assess for change over the 16-week intensive curriculum, 8-month boosters, and 18-month sustainability measures. A paired *t*-test will evaluate pre/post changes in continuous measures. 

Secondary associations considering participation in the TK-MT and the biometric data (change in body weight and clinically relevant change in one of the following metabolic markers: fasting plasma concentrations of glucose, insulin, triglyceride, cholesterol, HDL, LDL, and liver function as AST and ALT) will be analyzed using a linear mixed-effects regression model for continuous outcomes. 

Descriptive statistics (means, medians, proportions) will be used to summarize baseline characteristics and changes in these outcomes (self-reported health behaviors, lab values, and anthropometrics) over time. Baseline and demographic data will be controlled for in this model. Lastly, we will investigate whether missing data, due to dropouts and poor attendance, are non-ignorable through a sensitivity analysis based on the imputation approach developed by co-investigator [name] and colleagues [65]. Preliminary investigation of associations and correlations will be explored graphically and formally using parametric and nonparametric tests, as appropriate. Regression diagnostics will be performed to assess the validity of the multivariate models and their assumptions, and first-order interaction terms will be included to assess potential effect modification. 

For participant interviews and open-ended survey items, thematic analysis will be conducted by the HSPH team to independently read transcripts and conduct open and then focused coding using inductive and deductive coding approaches in NVivo (15, Lumivero, Denver, CO, USA) [66].

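### The 80%-power detectable rates in Table A1 hold only for 320 independent, fully followed people, while the plan describes shared classes and expected dropout

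*Protocol article*

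**What the plan says.** Section 2.3.2 states that 320 participants "will have 80% power to detect significant improvements in metabolic syndrome biomarkers ranging from 14.2 to 30.15" percent. Appendix A lists the inputs: two arms, "Total sample size is 320", "Two-sided test", "Under a significance level of 0.05", and a control improvement rate of 5% to 15%. The 320 comes from kitchen capacity: "20 study participants in the TK arm and 20 in the control group times two cohorts at each of four sites". Table A1 is headed as a two-sample test of proportions. No loss rate, ICC or design effect appears among the inputs.

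The same article describes group delivery. Classes are taught jointly by shared instructors (section 2.4.1), and peer influence is part of the mechanism: "Through group discussions and activities, participants learn from and motivate each other" (TK-MT Intervention Curriculum). Table 3 lists social influence and peer support in the behavioral framework. Controls have no classes until after the 12-month assessment (section 2.4.2).

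Section 2.7 plans to record withdrawal and attrition and to run a sensitivity analysis for data missing through dropout. It says the biometric outcomes "will be analyzed using a linear mixed-effects regression model for continuous outcomes", and does not list the random effects.

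**The concern.** This is an individually randomised trial in which one arm is treated in groups. Outcomes of people in the same class may be correlated, because they share instructors, peers and site arrangements. That correlation inflates the variance of the intervention-arm estimate and leaves the ungrouped control arm alone. Loss to follow-up shrinks both arms. A calculation that allows for neither gives the most favourable power that 320 people can yield.

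Two things are at stake. A null efficacy result could be read as coming from an adequately powered comparison when it did not. And the findings are meant to inform a larger trial (Introduction), so an independence-based calculation with no loss could be carried forward.

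**Working it through.** **Inputs from the document:** n = 160 per arm at 1:1; two-sided 0.05; control rate p0 = 5%, 10%, 15%; intervention rate p1 = 14.2%, 21.4%, 27.9% (Table A1, 1:1, power 0.8); 4 sites × 2 cohorts = 8 intervention groups of 20, taking one class group per site and cohort.

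**Assumed, because the document gives none:** loss d = 10% or 20%; intervention-arm ICC = 0.01, 0.02 or 0.05; no clustering among controls.

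**Step 1. Reproduce the plan.** With p̄ the mean of p0 and p1:

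Power = Φ[(p1 − p0 − 1.96·SE0)/SE1], SE0 = √[2p̄(1−p̄)/n], SE1 = √{[p0(1−p0) + p1(1−p1)]/n}.

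For 15% v 27.9%: SE0 = √(2 × 0.2145 × 0.7855/160) = 0.0459; SE1 = √[(0.1275 + 0.2012)/160] = 0.0453; (0.129 − 0.0900)/0.0453 = 0.86; power 80.6%. The other two rows give 80.1% (5% v 14.2%) and 80.3% (10% v 21.4%). The totals needed for exactly 80% are 320, 318 and 316, so the spare room is 0, 2 and 4 people, at most 4/320 = 1.25%. No allowance is hidden in the 320.

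**Step 2. Loss alone.** n = 160(1−d) = 144 or 128. Power over the three rows is 75.8–76.3% at 10% loss and 70.7–71.3% at 20%.

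**Step 3. Class clustering alone.** DE = 1 + (20−1)·ICC = 1.19, 1.38, 1.95, applied to the intervention arm only:

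SE0 = √[p̄(1−p̄)(1+DE)/n], SE1 = √{[p0(1−p0) + DE·p1(1−p1)]/n}.

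For 15% v 27.9% at ICC 0.02: SE0 = √(0.1685 × 2.38/160) = 0.0501; SE1 = √[(0.1275 + 1.38 × 0.2012)/160] = 0.0503; (0.129 − 0.0981)/0.0503 = 0.61; power 73.0%.

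**Step 4. Both.** At 20% loss, n = 128 and the mean class size is 16, so at ICC 0.02 DE = 1 + 15 × 0.02 = 1.30.

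| Assumption | 5% v 14.2% | 10% v 21.4% | 15% v 27.9% |
|---|---|---|---|
| None (as planned) | 80.1% | 80.3% | 80.6% |
| 10% loss | 75.8% | 76.0% | 76.3% |
| 20% loss | 70.7% | 71.0% | 71.3% |
| ICC 0.01 | 76.0% | 76.4% | 76.7% |
| ICC 0.02 | 72.2% | 72.7% | 73.0% |
| ICC 0.05 | 62.6% | 63.2% | 63.6% |
| 20% loss, ICC 0.02 | 64.2% | 64.6% | 64.9% |

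Solving the last row for 80% power gives detectable rates of about 16.7%, 24.1% and 30.8%.

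**Step 5. Few groups.** Steps 3 and 4 use normal critical values. With 8 groups the intervention-arm variance has about 7 degrees of freedom. For 15% v 27.9% at ICC 0.02 without loss, the arm variances are 1.38 × 0.2012/160 = 0.001735 and 0.1275/160 = 0.000797. Satterthwaite: df = 0.002532²/(0.001735²/7 + 0.000797²/159) ≈ 15, critical value about 2.13. Power is then Φ[(0.129 − 2.13 × 0.0501)/0.0503] ≈ 67%, not 73%. The clustered rows of the table are therefore optimistic.

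**Step 6. The other quoted rates.** Against control 15%, 30.15% is the 1:1 entry for 90% power, and 31.8% is the 90% entry for 0.7 allocation. By the same normal approximation at 1:1, 30.15% keeps 84% power at ICC 0.02 without loss, 80% at 20% loss with ICC 0.01, and 77% at 20% loss with ICC 0.02. For 31.8%, power is 84% at 20% loss with ICC 0.02.

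**Step 7. If class group were left out of the analysis.** Type I error = 2{1 − Φ[1.96/√((1+DE)/2)]} = 6.1%, 7.2% and 10.7% at ICC 0.01, 0.02 and 0.05.

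**The case against.** The strongest reply is that efficacy is a secondary, preliminary aim, that feasibility is primary and descriptive, and that 320 was set by kitchen capacity. That limits the consequence. It does not make a published 80% figure correct.

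A reader might infer that the design cannot deliver 80% at any rate the article quotes. The documents do not support that: as Step 6 shows, 30.15% and 31.8% keep about 80% or more in several scenarios.

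A reader might also infer that the analysis will ignore class grouping and so inflate type I error. Section 2.7 does not say so. It names a mixed-effects model that can carry such terms, and their specification may sit in an analysis plan that is not shown. The Step 7 figures are conditional only. A suitable model would protect type I error but would not restore power.

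Three further points stand in part.
- ICC and loss are assumed. The direction is documented; the size is not.
- Section 2.3.3 allows other group sizes and totals: roughly 4 × 28 = 112 to 8 × 30 = 240 per arm, reading the two-cohort range as per cohort. The upper end could absorb moderate loss. At 112 per arm power is about 65% even with independence and no loss. The power claim, however, is tied to 320.
- Table A1 concerns a yes/no improvement endpoint, while section 2.7 models continuous outcomes. The percentages here test the stated claim and are not the power of the planned model.

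Household members "must be randomized to the same study arm", which adds a little clustering, but the article does not say how many there will be. If 10% of participants were in pairs with correlation 0.3 (both assumed), the design effect would be 1 + 0.10 × 0.3 = 1.03, which is minor.

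**Conclusion.** The point holds for the 1:1, 80%-power entries of Table A1. Its arithmetic is right for its own assumptions, but the article contradicts those assumptions. Loss above about 1%, or any appreciable positive class correlation, takes power at these rates below 80%; that needs no outside figure. The size does. Loss of 10–20% alone gives about 71–76%, ICC 0.01–0.05 alone about 63–77%, and 20% loss with ICC 0.02 about 64–65%. All of these rest on a normal approximation with clustering in the intervention arm only, and those with clustering would be lower with degrees of freedom suited to 8 groups. Because efficacy is preliminary and secondary, this should be corrected but does not undermine the primary aim.

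**What to change.** - **Section 2.3.2 and Appendix A:** state that the present figures assume independence and complete follow-up. Restate the detectable rates as a range over a stated ICC (for example 0.01–0.05) and 12-month loss (for example 10–20%), computed with degrees of freedom suited to about 8 class groups. The 16.7%, 24.1% and 30.8% from Step 4 show the scale but are optimistic and should not be inserted as final. Label 30.15% and 31.8% as 90%-power entries, the latter from the 0.7-allocation row.
- **Section 2.7, or the analysis plan if it is set there:** include site and cohort, and a class-group random effect in the intervention arm only, in the mixed model already planned, with a small-sample correction such as Satterthwaite or Kenward-Roger. Report the observed ICC for the next trial.

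The cost is a less favourable stated detectable rate and slightly wider confidence intervals. No extra participants or data are needed.

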## Appendix B

**Table A2 nutrients-17-00314-t0A2:** TK-MT Intervention Curriculum Overview.

Class	Class Topic	Recipes ^a^	Culinary Skills/Techniques ^b^
1	Welcome Building a healthy plate/nutrition overview Pillars lifestyle change	Roasted veggie pasta	Knife skills intro Boiling pasta Roasting veggies
2	Vegetables and fruits Goals/wellness vision Intro to mindfulness	Shrimp and veggie stir fry	Stir-frying Hot oil/fire safety
3	Whole grains and carbs Intro to exercise	Farro salad and quick farro sauté (2 side dishes)	Grain cookery Making salads and vinaigrette Chopping and toasting nuts Sautéing veggies
4	Healthy fats and oils	Farmer salad with pan-seared salmon	Egg and fish cookery Making salads and vinaigrette Blanching
5	Protein—beans and legumes	(Turkey) veggie chili	Making chili/stew Making yogurt sauce Toasting spices Sautéing veggies
6	Protein—land animal/planetary health	Roasted chicken root veggie sheet pan	Sheet pan meals Roasting meat/veggies
7	Protein—seafood	Fish tacos (cod/tilapia or other white fish)	Making tacos and slaw Fish cookery—searing/sautéing Making yogurt sauce and vinaigrette
8	Dairy and fermented foods	Marinated tofu + asparagus	Cooking with tofu Yogurt sauce Marinating
9	Shopping and label reading Spices and hearty greens	Chana masala Garlicky greens	Making curry/stew Spices Sautéing veggies
10	Breakfast, sleep, and meal timing	Frittata (egg cups) Overnight oats—raspberry Yogurt parfait Maple granola	Egg cookery (baked) Hot cereals Baking/toasting No-heat cooking
11	Lunch, snacks, and managing stress	Kale salad Tuna niçoise sandwich Yogurt ranch + carrot	Making salads and vinaigrette Hearty greens Toasting nuts and grain cookery Egg cookery (boiling) Grating/microplaning
12	Dinner and shopping/meal planning	Black bean turkey burgers Roasted cauliflower and sweet potato	Roasting veggies and chopping herbs/garlic Blended burgers Yogurt sauce Searing/grilling meats
13	Desserts + drinks Added sugars, fructose, and artificial sweeteners	Baked apple—blueberry Harvest soup Infused water (demo)	Baking/grilling fruit Making soups Legume cookery Infusing water
14	Eating out and special occasions	Red lentil pasta w/marinara and garlic broccoli	Pasta cookery and making sauce
15	Modifying recipes (comfort foods)	Cauliflower quinoa mac and cheese	Making casseroles—baking Grain cookery Roasting veggies
16	Putting it all together—review and reflection	Grain bowl	Grain cookery Making dressing Marinating and searing meat/tofu Blanching, roasting, sautéing veggies/legumes
17	Motivations	Chipotle portobello tacos Mushroom focus Guacamole	Mushroom cookery, storage, and prep Roasting Knife skills
18	Meal planning revisited	Lemon fennel chicken skillet with whole wheat orzo	One pan skillet (braising and deglazing) Toasting grains
19	Activity/movement—beyond the basics	Fresh spring rolls w/peanut sauce No-bake energy bites Stuffed dates	Fresh herbs Canning/pickling Salad cookery and vinaigrette Cold grains
20	Revisiting sleep and stress	Sweet potato salmon croquette Simple green salad Spicy garlic aioli	Using canned fish Pan frying Making aioli Greens salad
21	Mindfulness and self-compassion	Thai tofu red curry Green option w/chicken	Rice cookery Stovetop curry Sauté
22	Gut health and immune system	Pickled red onion Tabouleh Roasted chickpeas	Roasting legumes Pickling Grain cookery
23	Healthy eating patterns for a lifetime	Turkey meatloaf Cauliflower smash Garlic-lemon sauteed green beans recipe	Baking meat Vegetable smash Sautéing
24	Celebration of accomplishments—review major concepts	Pizza party! Whole wheat pizza with homemade sauce Mocktail	They get options and can also pull from fridge Rolling dough Sauteing

^a^. All recipes are designed to serve 4 adults; ^b^. knife skills are covered in every class.

## Appendix C

### Development of the Curriculum

In order to construct a robust educational intervention that comprised culinary medicine along with lifestyle elements, a TK curriculum was created by thought leaders of the Teaching Kitchen Collaborative (TKC). Two multi-day meetings were held at the 1440 Multiversity in Scotts Dale, CA to co-create a curriculum using best practices from culinary medicine, lifestyle medicine, and research. The first meeting was attended by research directors of the TK clinical studies who developed the important research elements and additional educational outlines that would be covered in this TK curriculum. The second meeting was held with executive chefs from members of the TKC who created culinary competencies that they deemed essential for home cooking. The materials from these meetings were used by Harvard T.H. Chan School of Public Health, Dartmouth Hitchcock Health, and Maine General Health team members to create the initial 16-week intensive TK curriculum.

This was then pilot tested at Dartmouth Hitchcock Health Weight and Wellness Center in 2021–2022 to assess preliminary feasibility and acceptability of the intervention curriculum, assessment tools, and implementation of study components. Due to the COVID-19 pandemic, this study was modified from 100% in-person classes to 100% virtual classes. Edits were made to the curriculum based on pilot participant and staff feedback. This led to the current hybrid model that included two in-person classes to ensure all participants are able to gain safe knife skills training.
